## Abstract

**Background::**

The prevalence of excessive body weight has rapidly increased worldwide over the past decades; however, medications are intended for moderately and severely obese patients and are associated with side effects. As an alternative approach, the use of traditional herbal medicines has gained increasing popularity among overweight individuals in recent years in East Asia. HT048 is an herbal extract of *Citrus unshiu* and *Crataegus pinnatifida*, and HT077 is an herbal extract of *Nelumbo nucifera* and *Prunus persica*. These 4 herbs have been used widely for body weight reduction in China and Korea. The aims of this trial are to investigate whether HT048 and HT077 are effective at reducing body fat and weight in overweight adults, and to determine the safety of HT048 and HT077.

**Methods/design::**

A double-blind, randomized, placebo-controlled, 3-arm parallel group trial will be conducted in adults with a body mass index (BMI) of 25 to <30 kg/m^2^. A total of 120 eligible participants will be randomized in a 1:1:1 ratio to receive either HT048 (1000 mg), HT077 (400 mg), or matching placebo twice daily for 12 weeks, and will be monitored for an additional 4-week follow-up period after the treatment. All participants will be assessed for efficacy and safety of the investigational product at baseline and weeks 4, 8, 12, and 16. The primary endpoint is the change in body fat mass and percent body fat measured by dual-energy X-ray absorptiometry at week 12 from the baseline. The secondary efficacy variables are abdominal fat area measured by computed tomography, body fat mass and percent body fat measured by bioelectrical impedance analysis, body weight, BMI, and serum lipids and adipocytokines concentrations. Safety will be evaluated on the basis of reported adverse events, abnormal laboratory results, vital signs, and physical examination findings.

**Discussion::**

This is a first-in-human trial of HT048 and HT077 to assess the efficacy and safety in overweight subjects. The results will provide high-quality evidence of the therapeutic benefits of HT048 and HT077 for weight management and the prevention of obesity.

**Trial registration::**

Korean Clinical Research Information Service (KCT0004271) Registered September 2, 2019.

## Introduction

1

The prevalence of overweight and obesity has reached epidemic levels in developed countries. In South Korea, overweight and obese adults defined as having a body mass index (BMI) ≥25 kg/m^2^ were one-third of the total adult population in 2015 and are predicted to reach approximately 50% by 2030.^[1]^ Excessive body weight predisposes to or is associated with various complications such as cardiovascular diseases, type 2 diabetes, hypertension, certain cancers, and osteoarthritis in weight-bearing joints.

Conventional weight management programs such as dietary modification and physical activity generally have low adherence and success rates and have been reported to often result in weight cycling.^[2]^ Medications for obesity include a lipase inhibitor (orlistat), appetite suppressants (eg, phentermine, lorcaserin), and a glucagon-like peptide-1 receptor agonist (liraglutide). These drugs are intended for moderately and severely obese patients with a BMI ≥30 or a BMI ≥27 with comorbidities and are associated with a high incidence of side effects.^[3]^ As alternatives to these medications, complementary and alternative treatments, such as herbs and acupuncture, have gained increasing popularity among overweight and obese individuals in recent years.^[4]^ In particular, traditional herbal medicines have been widely used in Asian countries, including Korea and China, for weight reduction.^[4]^

HT048 is an herbal extract of *Citrus unshiu* peel and *Crataegus pinnatifida* fruit, and HT077 is an herbal extract of *Nelumbo nucifera* leaf and *Prunus persica* flower. HT048 and HT077 have been developed by screening medicinal herbs used in East Asia for obesity treatment, with the purpose of reducing body fat and weight.

*C unshiu* peel and *C pinnatifida* fruit have been widely used for hundreds of years in traditional Chinese and Korean medicine, and have attracted increasing attention as promising agents for the treatment and prevention of obesity and metabolic diseases.^[5,6]^ The antiobesity and lipid-lowering effects of the 2 herbs have been well documented in experimental studies.^[6–8]^ Furthermore, *C unshiu* lowered BMI and improved lipid profiles in overweight and obese subjects,^[9]^ and a *C pinnatifida*-based herbal formula reduced plasma low-density lipoprotein cholesterol levels in dyslipidemic patients.^[10]^ Our previous animal studies showed more effective reduction in high-fat diet-induced body weight gain when *C unshiu* and *C pinnatifida* were combined compared to the individual herb.^[11]^ Their combination, HT048, reduced body weight, and adiposity to levels comparable to those in the orlistat, an antiobesity drug, -treated group and improved dyslipidemia in obese rats.^[11]^

*N nucifera* leaf has been traditionally used as folk medicine for the treatment of obesity, hyperlipidemia, and hyperglycemia in China,^[12,13]^ and *P persica* flower has been consumed as a tea for weight reduction in China and Korea.^[14]^ In preclinical studies, *N nucifera* has been demonstrated to exert antiobesity effects by inhibiting carbohydrate and lipid absorption, stimulating lipolysis via β-adrenergic activation, increasing thermogenesis, and downregulating lipogenic genes.^[12,13,15–17]^ We reported that *P persica* reduces adiposity and hyperglycemia in obese mice and is more effective when combined with *N nucifera*.^[14,18]^ HT077, the combination of these 2 herbs, exerted antiobesity effects and decreased elevated triglycerides and glucose levels in mice fed a high-fat diet.^[18]^

Although traditional use and preclinical data support the clinical application of HT048 and HT077, a prospective randomized trial has yet to be performed to investigate the efficacy and safety of HT048 and HT077.

### Objectives

1.1

This study primarily aims to examine whether HT048 and HT077 are superior to the placebo in reducing body fat mass and percent body fat in overweight subjects. The secondary objectives are to assess the effects of HT048 and HT077 on abdominal fat, body weight, BMI, waist and hip circumference, and serum lipids and adipocytokines concentrations, and to investigate the safety of HT048 and HT077.

### Design

1.2

This study is a double-blind, randomized, placebo-controlled, superiority trial with 3 parallel groups. Eligible participants will be randomized in a 1:1:1 ratio to receive either HT048, HT077, or placebo for 12 weeks, and will be monitored for an additional 4-week follow-up period after the treatment.

## Methods and design

2

### Study setting

2.1

The participants will be recruited from the Department of Internal Medicine, Semyung University Korean Medicine Hospital (Jecheon, Chungcheongbuk-do, Republic of Korea). The first patient was enrolled on September 6, 2019 and the recruitment period is expected to be 6 months from September. The recruitment announcement will be posted on the hospital homepage and bulletin board of the hospital to reach the target sample size.

### Eligibility criteria

2.2

Participants who meet all the following criteria will be included.Men and women aged ≥19 and <60 years,BMI of 25 to <30 kg/m^2^,Participants who voluntarily decide to participate and sign the informed consent after being provided an explanation of this trial.

Participants who fall under any of the following conditions will be excluded.History of hypersensitivity to drugs or food ingredients,Participation in a commercial weight loss program or clinical trial for obesity within the last 3 months,Taking drugs or diet foods that affect their weight within 3 months before screening,Intentional weight loss of at least 5% within 3 months before screening,Undergone surgery, such as gastroplasty and intestinal resection, to lose weight within 6 months before screening,Endocrine diseases such as hypothyroidism and Cushing syndrome,Severe cerebrovascular disease (cerebral infarction, cerebral hemorrhage, etc), heart disease (angina pectoris, myocardial infarction, heart failure, arrhythmia in need of treatment), and lung disease (chronic obstructive pulmonary disease, etc) within the last 6 months. (However, those who are clinically stable may participate in the trial at the investigator's discretion),Serious dysfunction of the liver (alanine and aspartate aminotransferase levels of 2.5 times the upper limit of normal) or kidney (creatinine >2.0 mg/dL),Uncontrolled hypertension (blood pressure ≥160/100 mm Hg),Fasting blood glucose ≥126 mg/dL or random blood glucose ≥200 mg/dL, or diabetic patients taking oral hypoglycemic agents or insulin,Malignant tumor diagnosed within 3 years before screening,Complaint of severe gastrointestinal symptoms such as heartburn and indigestion,Psychologically significant medical history or current disease (schizophrenia, epilepsy, anorexia, bulimia, etc), or a history of alcohol or drug abuse,Determined to be unable to exercise because of musculoskeletal disorders,Pregnant or lactating women, or women of childbearing age who do not agree to use contraception during the trial,Participants who are deemed unable to comply with the test requirements or otherwise deemed unsuitable according to the investigator's opinion.

### Procedures

2.3

This trial is designed to provide a 12-week treatment with either HT048, HT077, or placebo in overweight subjects and assess the reduction in body fat and weight for 16 weeks. The trial flow diagram is presented in Figure 1 and the schedule for enrollment, interventions, and assessment of this study is shown in Table 1. The principal investigator will obtain written informed consent from subjects who voluntarily agreed to participate in the study. Participants will be assessed for eligibility through screening tests at the first visit. Participants who meet the inclusion and exclusion criteria will undergo baseline assessments within 14 days after screening. At the baseline visit, participants will be randomly assigned to 1 of 3 groups: HT048, HT077, or placebo groups, with a 1:1:1 allocation ratio and will receive investigational products for 12 weeks. Participants will visit the hospital at weeks 4, 8, and 12 during treatment and will attend a follow-up visit 4 weeks after completing the treatment (at week 16). Efficacy and safety assessments will be conducted at baseline and weeks 4, 8, 12, and 16 as indicated in Table 1. All efficacy assessment items, including dual-energy X-ray absorptiometry (DXA), abdominal computed tomography (CT), bioelectrical impedance analysis (BIA), body weight, BMI, waist and hip circumference, and serum lipids and adipocytokines concentrations, will be performed on an empty stomach. Dietary intake and physical activity will be assessed using 24-hours dietary recall and international physical activity questionnaire short form, respectively, at baseline and weeks 12 and 16.

**Figure 1 F1:**
[figure not shown]
The study flow diagram. ^∗^The number of participants expected to complete the study.

**Table 1 T1:**
[figure not shown]
The schedule of enrollment, interventions, and assessments.

### Interventions

2.4

The investigational product will be produced by COSMAX BIO Inc (Jecheon, Chungcheongbuk-do, Republic of Korea). The active product is a 500 mg tablet containing either 333.3 mg HT048 (125.8 mg of *C unshiu* extract and 207.5 mg of *C pinnatifida* extract) or 133.3 mg HT077 (57.3 mg of *N nucifera* extract and 76.0 mg of *P persica* extract). The active and placebo tablets are identical in shape, size, and color. Participants will be orally administered either 3 active or placebo tablets per dose, twice a day (morning and evening after meals) for 12 weeks. The daily doses are 2000 and 800 mg for HT048 and HT077, respectively. Participants will receive a 1-month supply of investigational product at baseline and weeks 4 and 8 and will be encouraged to continue to follow the prescribed dosage regimen. At weeks 4, 8, and 12, unused tablets will be returned and counted for the evaluation of participants’ compliance.

Participants will be advised to maintain their usual diet and exercise levels during the study. Participants will be prohibited to receive medicines and functional foods that can affect body weight and body fat during the study. Medicines, functional foods, exercise therapy, and diets that participants previously maintained before enrollment may be allowed if necessary at the investigator's discretion. Information regarding all concomitant medications, including the product or ingredient name, dosage, and duration, will be recorded at every visit.

Intervention will be discontinued under the following circumstances:(1)if a serious adverse event occurs;(2)if a participant has used a drug or physical procedure that could affect body weight and body fat;(3)if a participant wish to discontinue study participation;(4)if difficulties in assessments occur owing to administrative reasons, such as violations in dosage method or visit schedule; and(5)if difficulties in follow-up occur owing to a participant's personal reasons.

### Randomization and blinding

2.5

Participants determined to be eligible for this study will be randomly assigned to the HT048, HT077, or placebo groups in a 1:1:1 ratio using a computerized block randomization method. An independent statistician will generate the randomization sequence number and the block size will not be disclosed to the investigator for allocation concealment. Participants will be assigned a randomization number consecutively in the order in which they are enrolled and will receive the investigational product labeled with the same randomization number throughout the trial. The packaging and labels of investigational products for the 3 groups will remain the same for blinding purposes. Participants and all research personnel will be blinded to the assignment. The randomization sequence will be concealed in sealed opaque envelopes and will not be disclosed to the investigator until the end of the study, except when inevitable, such as when serious adverse events occur. If a code break occurs, the investigator will notify the contract research organization and the sponsor immediately and record the date and reason for the code-break in the case report form.

### Outcome measures and endpoints

2.6

DXA will be used to assess body fat mass and percent body fat at baseline and week 12 as the primary outcome measure. In addition, body fat mass and percent body fat will be measured by BIA at baseline and weeks 4, 8, and 12. DXA and BIA are representative methods for assessing body composition, and the correlation between the 2 measurements for body fat mass and percent body fat are generally known to be good in both sexes.^[19,20]^ Abdominal CT will be used to measure visceral fat area, subcutaneous fat area, total abdominal fat area, and visceral fat/subcutaneous fat area ratio at baseline and week 12. CT scanning will be performed between the fourth and fifth lumbar vertebrae. With high accuracy, CT is considered as the reference method for measuring visceral and subcutaneous fat.^[21]^ Body weight and BMI will be measured at baseline and weeks 4, 8, 12, and 16. Waist circumference, hip circumference, and waist circumference/hip circumference ratio will be assessed at baseline and weeks 4, 8, and 12. According to the World Health Organization guidelines, waist circumference will be measured at the midpoint between the lower margin of the last palpable rib in the midaxillary line and the top of the iliac crest, and hip circumference will be measured at the largest circumference of the buttocks.^[22]^ Serum lipids (total cholesterol, triglyceride, high density lipoprotein cholesterol, and low-density lipoprotein cholesterol) and adipocytokines (leptin and adiponectin) concentrations will be assessed at baseline and week 12.

The primary efficacy endpoint is the change in body fat mass and percent body fat measured by DXA at week 12 from the baseline. The secondary efficacy endpoints are as follows:(1)the change in body fat mass and percent body fat measured by BIA at weeks 4, 8, and 12 from the baseline;(2)the change in visceral fat area, subcutaneous fat area, total abdominal fat area, and visceral fat/subcutaneous fat area ratio measured by abdominal CT at week 12 from the baseline;(3)the change in body weight at weeks 4, 8, and 12 from the baseline;(4)the change in BMI at weeks 4, 8, and 12 from the baseline;(5)the change in waist circumference, hip circumference, and waist circumference/hip circumference ratio at weeks 4, 8, and 12 from the baseline;(6)the change in blood lipids (total cholesterol, triglyceride, high density lipoprotein cholesterol, and low-density lipoprotein cholesterol) concentrations at week 12 from the baseline;(7)the change in serum leptin and adiponectin concentrations at week 12 from the baseline;(8)the change in body weight at week 16 from week 12; and(9)the change in BMI at week 16 from week 12.

Safety will be assessed on the basis of adverse events reported by participants or the principal investigator, abnormal laboratory results (hematology, biochemistry, and urinalysis), vital signs, and physical examination findings. Laboratory tests will be performed at screening, baseline, and week 12. Measurements of vital signs and physical examination will be performed at every visit.

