### Sample size

2.7

This study aims to determine whether HT048 and HT077 is superior to placebo in reducing the change in percent body fat as measured by DXA at 12 weeks after the baseline measurement. The sample size has been estimated based on a previous study that evaluated the efficacy of an herbal extract powder for body fat reduction in overweight adults with a BMI of 25.0 to 29.9 kg/m^2^.^[23]^ The mean changes in percent body fat after the 12-week administration period are hypothesized to be 2.2% and 0.5% in the treatment and placebo groups, respectively, and the pooled standard deviation is hypothesized to be 2.14. Therefore, 25 participants in each group are needed to achieve a statistical power of 80% with a 2-sided significance level of 5%. To increase the power of the study, the sample size will be increased by 28%, with 32 participants in each group. Considering a drop-out rate of 20%, a total of 120 participants, 40 in each group, will be included in this study.

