### Statistical analysis

2.8

The efficacy outcome data will be analyzed by using both intention-to-treat and per-protocol population. The intention-to-treat population will comprise all randomized participants and the per-protocol population will be composed of participants whose primary efficacy assessments were performed according to the protocol without major protocol violations, such as unmet inclusion/exclusion criteria or the use of prohibited medication. Participants whose compliance to treatment is less than 80% will be excluded from the per-protocol population. The safety outcome data will be analyzed by using a safety population, which will include participants who receive treatment at least once and have at least 1 safety assessment after treatment. Missing data will be replaced using the last observation carried forward method.

Continuous variables will be described as mean, median, standard deviation, and range (minimum and maximum), and categorical variables will be described as frequency and percentage. Analysis of covariance with the baseline measurements as a covariate will be performed to examine inter-group differences in the primary and secondary endpoints. Continuous variables will be compared by using an independent *t* test or Wilcoxon rank-sum test between the treatment and placebo groups, depending on normality of the distribution. In addition, differences within groups before and after the intervention will be compared by using a paired *t* test or Wilcoxon signed-rank test. Categorical variables will be presented as the frequency and percentage and compared by using either the Chi-square or Fisher exact test. Adverse events will be classified by the Common Terminology Criteria for Adverse Events from the National Cancer Institute (ver. 4.0). Probability values of <.05 with 2-tailed tests will be considered significant. The statistical analysis will be performed with SPSS Statistics software version 25 (IBM, Chicago, IL). No interim analyses will be performed.

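### Two DXA measures are primary but only percent body fat is sized, and nothing says whether one or both must reach p<.05 or how the two products share the 5%

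*Protocol article*

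**What the plan says.** Section 1.1 (Objectives) says the study "primarily aims to examine whether HT048 and HT077 are superior to the placebo in reducing body fat mass and percent body fat". Section 2.6 (Outcome measures and endpoints) repeats this: "The primary efficacy endpoint is the change in body fat mass and percent body fat measured by DXA at week 12". The Abstract defines the primary endpoint in the same way. Two products and two measures give four comparisons with placebo.

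Section 2.7 (Sample size) puts the aim differently. It asks whether the products are "superior to placebo in reducing the change in percent body fat as measured by DXA", and body fat mass does not appear. The calculation takes mean changes of 2.2 and 0.5, a pooled SD of 2.14, 80% power and a two-sided 5% level. It arrives at 25 per group, raised by 28% to 32 in order to increase power, and then to 40 per group (120 in total) for 20% drop-out.

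Section 2.8 (Statistical analysis) says: "Analysis of covariance with the baseline measurements as a covariate will be performed to examine inter-group differences in the primary and secondary endpoints". It adds: "Continuous variables will be compared by using an independent *t* test or Wilcoxon rank-sum test between the treatment and placebo groups". Its only significance rule is: "Probability values of <.05 with 2-tailed tests will be considered significant".

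**The concern.** The sections do not describe the same primary hypothesis. Sections 1.1 and 2.6 have two measures per product; section 2.7 has one. Under the uniform threshold in section 2.8, a reader of the final report could not tell what counted as success.

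The two possible rules have opposite consequences. If a product succeeds on either measure, the 5% level is exceeded for that product. If it must succeed on both, the level holds per product, but the stated sample size does not address that criterion. Separately, two products share one placebo group and each is tested at the full 5%. The article does not say whether they are one family or two separate claims.

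**Working it through.** **Inputs from section 2.7:** difference 2.2 − 0.5 = 1.7; SD 2.14; two-sided 5%; power 80%; 32 completers per group.

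**Reproducing the plan's figure.** n per group = 2 × [SD × (1.960 + 0.842) / difference]² = 2 × (2.14 × 2.802 / 1.7)² = 24.88, rounded up to 25. Then 25 × 1.28 = 32; 32 / 0.80 = 40; 3 × 40 = 120. The arithmetic is right. It is the size for one two-arm test of one measure at an unadjusted 5%.

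**Type I error, no true effect on either measure.** The correlation r between the changes in the two measures is not in the article, so a range is assumed. Two product-placebo contrasts sharing a placebo group of equal size have correlation 0.5.

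- Either measure, one product: 0.05 + 0.05 − P(both significant).
- Both measures, one product: P(both significant), from the bivariate normal.
- Across both products: simulation of three arms and two measures, 1,000,000 replicates per r.

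| r | Either measure, per product | Either measure, any success across both products | Both measures, per product | Both measures, at least one product |
|---|---|---|---|---|
| 0.5 | 9.1% | 16.2% | 0.9% | 1.8% |
| 0.7 | 8.3% | 14.8% | 1.7% | 3.1% |
| 0.8 | 7.8% | 13.9% | 2.2% | 4.1% |
| 0.9 | 7.0% | 12.6% | 3.0% | 5.5% |
| 0.95 | 6.5% | 11.6% | 3.5% | 6.5% |

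For two products on one measure: 0.05 + 0.05 − 0.009 = 9.1%. These rates count significance in either direction, as the two-sided 5% does. In favour of a product only, the any-success figures are 8.1% at r = 0.5 and 5.8% at r = 0.95, against a nominal 2.5%.

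**Power at 32 completers per group.** Non-centrality = 1.7 / (2.14 × √(2/32)) = 1.7 / 0.535 = 3.18, with 62 degrees of freedom. The non-central t gives:

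- 5% per test: 87.9%
- about 2.7% (Dunnett, two contrasts): 81.7%
- 2.5% (Bonferroni, two products): 80.8%
- 1.25% (Bonferroni, four tests): 72.6%

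Under Holm over the two products, if both work, simulated power per product is about 85% to 86%.

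**Power if both measures must succeed.** This needs an effect for body fat mass, which the article does not give. If its standardized effect equals that of percent body fat (1.7 / 2.14 = 0.79), power per product at 5% runs from about 80% at r = 0.5 to 85% at r = 0.95 with t tests (81.5% to 86.4% by the normal approximation).

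**The case against.** The strongest case is that the article condenses a full protocol that is not shown. Multiplicity rules often sit in that document or in the analysis plan, and the p<.05 line may be no more than a general convention. That stands as far as silence goes: the absence of an adjustment procedure would not by itself be a finding. It does not cover the disagreement between sections 2.6 and 2.7 on what is primary, which is in the printed text.

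Second, a reader might infer that the trial as planned has a 12% to 16% false-positive rate. The article does not support that. It nowhere says that any one of the four tests makes the trial positive, and section 2.6 speaks of one endpoint in the singular, with the two measures joined by *and*. Requiring both is a plausible reading, and under it the error per product stays below 5%. That reading is not stated either, and section 2.7 does not follow it.

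Third, HT048 and HT077 are different extracts, each with its own comparison with placebo. Whether such products need one shared 5% is debated among statisticians, so adjustment across products is partly a matter of choice. The article should still say which position it takes.

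Finally, the ANCOVA might be meant as an overall three-group test that comes first. Section 2.8 describes no such gate, and the superiority aim is product against placebo.

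**Conclusion.** The concern holds as an unresolved definition of success. Two measures are primary in the Abstract and sections 1.1 and 2.6, one is named and sized in section 2.7, and section 2.8 applies a single threshold to all tests. The consequence depends on a rule the article does not give. With either measure sufficient, the error per product is about 9% to 6.5%. With both required, it is controlled per product, but the power is unstated because nothing is assumed for body fat mass. All the ranges rest on an assumed endpoint correlation of 0.5 to 0.95.

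It would go too far to call the sample size wrong or too small. Its arithmetic reproduces, and the step from 25 to 32 per group is about what either a split over two products or a both-measures rule needs; the latter also assumes an equal standardized effect on body fat mass. This should be fixed, but it does not invalidate the design.

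**What to change.** Before unblinding, reconcile sections 1.1, 2.6 and 2.7 in one of two ways:

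- **(a) One primary endpoint.** Make percent body fat by DXA at week 12 the single primary endpoint. Test body fat mass for a product only after that product has succeeded on percent body fat.
- **(b) Co-primary endpoints.** State that a product succeeds only if both measures reach p<.05. Add to section 2.7 the assumed effect and SD for body fat mass and the joint power (about 80% to 86% per product at 32 per arm if the standardized effects are equal).

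Then state in section 2.8 how the two products share the 5%. With Holm or Dunnett on one primary endpoint, 32 completers per arm give about 81% power per product at two-sided 2.5%, and about 85% to 86% under Holm if both products work, against 88% unadjusted. If each product is instead a separate claim at 5%, say so and acknowledge the chance of at least one false success: roughly 9% under (a), and 1.8% to 6.5% under (b). If (b) is combined with a split across products, its power has to be computed and stated, since it will be lower than the figure given in (b).

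The cost is wording in the protocol and analysis plan and, where the level is split, a somewhat lower stated power. No more patients are needed under (a), or under (b) with each product at 5% if the standardized effects are equal.

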Despite these limitations, one of the major strengths of this study lies in its prospective, double-blind, randomized, placebo-controlled design. Furthermore, BIA, DXA, and abdominal CT will be used to evaluate the efficacy of fat loss, thereby yielding more accurate and comprehensive results. BIA is simple, noninvasive, and inexpensive, but tends to underestimate body fat in overweight and obese subjects.^[20,24]^ Compared with BIA, DXA has greater accuracy and allows not only the quantification whole body fat, but also regional (ie, android, gynoid, trunk, arms, and legs) estimates of fat compartment.^[25]^ Visceral adiposity plays an important role in the pathogenesis of metabolic syndrome and is an independent predictor of mortality.^[26–28]^ CT allows visceral fat to be distinguished from subcutaneous fat with a greater precision than DXA and is considered the reference standard for the measurement of visceral adipose tissue.^[21]^ In addition, participants will be monitored for an additional 4-week follow-up period after the 12-week treatment to evaluate the maintenance of efficacy and safety. Some antiobesity mechanisms, such as appetite suppressants, can lead to withdrawal symptoms,^[29]^ but many herbal medicines lack follow-up studies after the end of administration.

This study is a first-in-human trial of HT048 and HT077 in overweight subjects. The results of this trial, which has a stringent design and high methodological quality, will provide evidence of the therapeutic benefits of HT048 and HT077 for weight management and the prevention of obesity.

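### The follow-up is meant to assess maintenance, but the only week-16 endpoints measure change from week 12; no comparison of the arms from baseline to week 16 is planned

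*Protocol article*

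**What the plan says.** The Discussion states that participants are followed for 4 weeks after treatment "to evaluate the maintenance of efficacy and safety". Section 2.3 (Procedures) says that the trial will "assess the reduction in body fat and weight for 16 weeks".

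Section 2.6 (Outcome measures and endpoints) lists nine secondary efficacy endpoints. Only the last two use week 16: item 8, "the change in body weight at week 16 from week 12", and item 9, "the change in BMI at week 16 from week 12". The endpoints referenced to baseline end earlier: item 3 is "the change in body weight at weeks 4, 8, and 12 from the baseline" and item 4 is "the change in BMI at weeks 4, 8, and 12 from the baseline". The measurements themselves run further: "Body weight and BMI will be measured at baseline and weeks 4, 8, 12, and 16".

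No body-fat measurement is scheduled at week 16 in section 2.6. DXA is done at baseline and week 12, and "body fat mass and percent body fat will be measured by BIA at baseline and weeks 4, 8, and 12".

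Section 2.8 (Statistical analysis) applies analysis of covariance, with the baseline measurement as covariate, to between-group differences in primary and secondary endpoints. It uses a two-sided 5% level and fills missing data by LOCF.

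**The concern.** Maintenance asks whether the product arms are still better than placebo four weeks after stopping, measured from where everyone started. Items 8 and 9 ask something else: how much weight changed after stopping. Their starting value, week 12, has already been affected by treatment. An arm that lost more has more to regain, so a product with real remaining benefit can come out worse than placebo on the only between-arm comparison at week 16. A product that did nothing and a product whose benefit was fully kept both give a difference of zero.

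At stake is the reading of the follow-up phase. Section 2.8 would test items 8 and 9 between groups, and a significant result in favour of placebo could be reported as loss of efficacy when it reflects partial rebound from a larger loss. The LOCF rule adds a second difficulty, because a missing week-16 weight is set to the week-12 weight and so counts as no regain.

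**Working it through.** **Plan's own figures.** The article gives no figure for the week-16 endpoints. Its sample size (section 2.7) reproduces: 2 × (1.96 + 0.84)² × 2.14² / 1.7² rounds up to 25 per group; 25 × 1.28 = 32; 32 / 0.8 = 40; 3 × 40 = 120. This point does not affect it. The 32 per group is used below.

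**Identity.** For each participant, change from baseline to week 16 = (change from baseline to week 12) + (change from week 12 to week 16). The plan tests each part but not the sum.

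**General result.** Let the product arm lose D kg more than placebo by week 12, and let both arms regain the same fraction r of their loss.

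- Week-12-to-16 difference, product minus placebo: +r × D (positive means product worse).
- Baseline-to-week-16 difference: −(1 − r) × D (negative means product better).

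The signs are opposite for every r strictly between 0 and 1. At r = 0 the first difference is zero for any D, including D = 0.

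**Illustration.** Assumed week-12 losses are 2.0 kg (product) and 0.5 kg (placebo), so D = 1.5 kg.

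| r | Week 12 to 16 | Baseline to week 16 |
|---|---|---|
| 0 | 0 | −1.5 kg |
| 0.25 | +0.375 kg | −1.125 kg |
| 0.5 | +0.75 kg | −0.75 kg |
| 1 | +1.5 kg | 0 |

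Range: at r = 0.5, with assumed product losses from 1.5 to 3.0 kg, the week-12-to-16 difference runs from +0.5 to +1.25 kg and the baseline-to-week-16 difference from −0.5 to −1.25 kg.

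**How often a test would mislead.** This simulation used 4,000 trials per setting, 32 per arm, the losses above, and an unadjusted t test. It assumed an SD of 2.0 kg for the change to week 12 and 1.0 kg of added noise from week 12 to 16.

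| r | Product significantly worse, week 12 to 16 | Product significantly better, baseline to week 16 |
|---|---|---|
| 0 | 2% | 76% |
| 0.25 | 26% | 69% |
| 0.5 | 57% | 55% |

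Check at r = 0.25:

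- Week 12 to 16: SD = √(0.25² × 2.0² + 1.0²) = 1.118, SE = 1.118 × √(2/32) = 0.28, and 0.375 / 0.28 ≈ 1.34.
- Baseline to week 16: SD = √(0.75² × 2.0² + 1.0²) = 1.803, SE = 0.45, and 1.125 / 0.45 ≈ 2.5.

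Both ratios agree with the simulated rates. Adjusting for the baseline value does not change the argument, because the week-12 value is still subtracted.

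**LOCF.** If a fraction q of an arm is missing at week 16 and those participants would have regained m kg on average, LOCF understates the arm's mean regain by q × m. Suppose missing participants would have regained 0.5 kg, like the others. A true mean of 0.5 kg then appears as 0.45 kg at q = 0.1 and 0.40 kg at q = 0.2. If they would have regained nothing, there is no understatement. The week-16 missing rate is not stated, so q is an assumption.

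**The case against.** Several points on the other side stand.

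- Change from week 12 to 16 answers a legitimate question. The Discussion mentions withdrawal effects after some antiobesity mechanisms and the lack of post-treatment follow-up for many herbal medicines. Greater regain in the arm that lost more is what a rebound measure should show.
- A reader might infer that the trial cannot show whether benefit persists. The documents do not support that. Adding the mean changes in items 3 and 8 gives the mean change from baseline to week 16. What is missing is a planned test or interval for that sum.
- A reader might also infer selection bias from the week-12 starting point. The intention-to-treat population keeps all randomised participants, so the difference validly estimates the effect on post-treatment change. The fault lies in what that difference is taken to mean.
- The misleading reading needs some regain, and its size here rests wholly on assumed losses and regain.
- The 20% drop-out in section 2.7 serves the week-12 sample size. It should not be read as the week-16 missing rate.
- The section 2.3 sentence is a one-line overview that defers to Table 1, whose content was not available for this check. Its mention of body fat over 16 weeks is loose wording without analytic consequence.
- Maintenance is not among the objectives in section 1.1, and an analysis plan not shown could add the contrast.

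These points limit the size of the finding but do not remove it. The article states a purpose for the follow-up and lists its endpoints, and none of them compares the arms from baseline to week 16.

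**Conclusion.** The point holds in a limited form. The stated week-16 endpoints measure rebound and do not by themselves test whether benefit persists, although the data for that comparison are collected. With equal proportional regain, the week-12-to-16 comparison favours placebo by r × D while the product keeps an advantage of (1 − r) × D from baseline. Under the assumptions shown, with 25% regained, that is 0.375 kg against the product and 1.125 kg still in its favour. With no regain the comparison is zero whether or not the product worked.

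LOCF understates regain by an amount that depends on the unstated week-16 missing rate and on how missing participants would have fared. The finding concerns secondary endpoints only; the primary endpoint, sample size and week-12 conclusions are unaffected.

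**What to change.** 1. In section 2.6, add change in body weight and in BMI from baseline to week 16 as the maintenance endpoints, adjusted for the baseline value, with each product compared with placebo and an interval reported.
2. For these endpoints, handle missing week-16 values with a likelihood-based repeated-measures model on weeks 4, 8, 12 and 16. Carrying week 12 forward would credit the participant with the whole week-12 change at week 16.
3. Keep items 8 and 9 as rebound measures, read alongside the baseline-to-week-16 result.
4. Align the overview sentence in section 2.3 with the schedule in section 2.6, which has no body-fat measurement at week 16. The correction should not say that week 16 covers weight and BMI only, because diet, physical activity, vital signs and physical examination are also assessed then.

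Cost: no new visit, measurement or participant. The protocol is already approved and registered and enrolment has begun, so a minor amendment is needed, preferably before unblinding.
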